### **Mechanistic Component**

- Group 1 (Muscular Effects):
  - The primary dependent variable (DV) for this group is asymmetry in skeletal muscle proton transverse relaxation time (T2) of the lumbar muscles. Our pilot study (n=9) indicates that the primary difference in this outcome is 22.7% asymmetry observed at baseline.[18] Following a manual therapy treatment that included a combination of manipulation and mobilization techniques we observed a reduction in T2 asymmetry to 6.0% immediately following treatment and T2 asymmetry remained reduced (9.4% asymmetry) 2-days post-treatment with a residual standard deviation of 12.8. For this analysis, these values were used as population means. While the mean T2 asymmetry level for 4-weeks post-treatment is unknown, for our power analysis we assume an asymmetry value of 15.0%. For the mobilization treatment arm we assumed T2 asymmetry levels of 22.7%, 7.7%, 10.7%, and 16.7% at baseline, immediately following treatment #1, 2-days following a course of treatment, and 4-weeks post course of treatment, respectively. The rationale for these predicted group differences are based on our recent work suggesting that the cavitation (i.e., audible 'pop') associated with manipulation results in larger physiological changes (i.e., changes in stretch reflex excitability). Given that cavitation is less likely to occur with joint mobilization, we assume

smaller physiological effects from this treatment. For the Sham Control group, we set the baseline mean at the same 22.7% and a placebo effect of ~5%; that is, the population mean T2 asymmetry level for this groups at subsequent measures were set at 21.7%.

- Our simulation studies indicate that 14 participants in each of the 3 Groups were sufficient to achieve power of 0.80 to detect a significant Group effect either immediately following treatment #1, 2-days following a course of treatment, or 4-weeks post course of treatment given an attrition rate of 10% and appropriate alpha adjustments.
- Group 2 (Spinal Effects):
  - The primary dependent variable (DV) for this group is the short-latency stretch reflex amplitude. Our preliminary work indicates that spinal manipulation reduces stretch reflex amplitude in individuals with chronic LBP who exhibit an audible joint sound by 30% from 0.56 to 0.39.[61] In study participants with no audible joint sound, there was a non-significant 10% increase from 0.62 to 0.68. The baseline standard deviation was 0.25 for both groups. We assumed manipulation would result in a 25% reduction 2-days following a course of treatment and a 20% reduction 4-weeks post course of treatment. Given our pilot data indicating the importance of cavitation, we assumed smaller reductions in stretch reflex amplitudes at each time point for the joint mobilization treatment arm. (i.e., 28, 23, and 18% reductions at the three endpoints). Finally, we assumed that Sham Control would have the same mean (0.68) at each testing point.
  - Our simulation studies indicate that 20 participants in each of the 3 Groups were sufficient to achieve power of 0.80 to detect a significant Group effect either immediately following treatment #1, 2-days following a course of treatment, or 4-weeks post course of treatment given an attrition rate of 10% and appropriate alpha adjustments.
  - See appendix for sample size and randomization regarding supplemental research
- Group 3 (Cortical Effects):
  - Changes in cortical excitability following manual therapy treatments are assumed to follow our observed changes in spinal reflex excitability. Accordingly, we assume the same magnitudes of changes for these DV's as detailed above. Specifically, we assume a 30%, 25%, and 20% reduction in measures of intracortical excitability in the manipulation treatment arm immediately following treatment #1, 2-days following a course of treatment, and 4-weeks post course of treatment, respectively. Likewise, we assumed 28%, 23%, and 18% reduction for the mobilization treatment arm, and no change for the sham treatment arm. The residual variance was set at 50% of the initial value, similar to the Group 2 variables.
  - Our simulation studies indicate that 20 participants in each of the 3 Groups were sufficient to achieve power of 0.80 to detect a significant Group effect either immediately following treatment #1, 2-days following a course of treatment, or 4-weeks post course of treatment given an attrition rate of 10% and appropriate alpha adjustments.

### **Sample Size for RCT Component**

Our co-primary outcomes are NPR and RMDQ at the primary endpoint (i.e., 3-days +/-1-day following a course of treatment). As stated previously, we will collapse the clinical outcome data across the three physiological outcome groups for a total sample size of 54/treatment arm. A recent review of a large number of RCTs on the effects of spinal manipulation for the treatment of chronic low back pain indicate that small treatment effect sizes are observed.[62] However, the effect sizes reported for studies that used a clinical prediction rule to identify individuals most likely to respond to manipulation treatment report large effect sizes. (e.g., effect size  $d > 1.3$  for clinically meaningful reductions in disability).[63] The RELIEF Study will use a modified-clinical prediction rule to define a target population of patients with chronic low back pain who are most likely to respond to manual therapy treatment. However, because our population is chronic

rather than acute (a factor in the original clinical prediction rule) we took a more conservative approach and based our power calculations on the assumption of a moderate treatment effect (i.e., effect size  $d=0.5$ ) to reduce disability.

- Our calculations are based on an assumed moderate effect size (effect size  $d=0.5$ ; based on data from Maughan and Lewis' work indicating standard deviations for NPR being 2.5 and RMDQ being 6 for patients with chronic low back pain).[64] Our simulation studies indicate that 54 subjects/treatment arm is sufficient to achieve power of 0.80 to detect a significant treatment effect at our primary endpoint (i.e., 2-days following the course of treatment) given an attrition rate of 10% and appropriate alpha adjustments. With this sample size we have sufficient power to detect changes in  $NPR > 2$  and  $RMDQ > 3$ , which are the classically defined levels of clinically-meaningful important differences in these outcomes.

### Treatment Assignment Procedures

Randomization & Stratification: The study statistician will use the R statistical language to block-randomize treatments stratified by sex for each of the three separate experiments. Specifically, within each experiment there will be two strata within which we will create variable blocks of 3 or 6 patients, where treatments are permuted. Then the study coordinator will assign subjects to the treatment arms. In instances where multiple experiments are actively enrolling study participants and a participant meets eligibility requirements for *more than one experiment*, we will then use an adaptive randomization method to allocate them to one of the experiments. This method ensures that an experiment with fewer participants enrolled will have a higher allocation ratio. Specifically, with two potential experiments, the allocation ratio for Experiment  $i$  ( $p_i$ ) will be  $p_i = 1 - n_i/N$ , where  $n_i$  is the sample size for Experiment  $i$  and  $N$  is the total sample size thus far enrolled. With three active experiments, the allocation ratio will be  $p_i = (1 - n_i/N)/2$ . Note that this process would occur prior to the randomization to a treatment arm.

- Masking or Blinding: In the RELIEF Study the principal investigators, the statistician, and members of the data collection team will remain blinded to intervention assignment throughout the duration of the study. They will be given the identifying codes only at the end of the study when it is necessary to interpret the results of the study. The un-blinded study coordinator, who is responsible for scheduling testing and treatment sessions, will serve to receive the study patients and escort them to the various testing and treatments sites to minimize the interaction between patients; however, the study coordinator will not participate in the assessments.

### 9.3 Interim Analyses and Stopping Rules

No interim analyses are planned as they relate to either the primary or secondary outcome data. An individual subject would be discontinued from the study intervention if a medical condition develops that precludes the continuation of the treatment intervention. Additionally, the study will be stopped if the IMC, in consultation with NCCIH, decides that the risks associated with the treatment interventions (i.e., excessive SAEs) outweigh the potential benefits of the knowledge gained from continuing the study.

### 9.4 Outcomes

The primary outcome variables for both components are provided below.

#### Mechanistic Component

- Group 1 (Muscular Effects):
  - Skeletal muscle proton transverse relaxation time (T2) of the lumbar muscles.
- Group 2 (Spinal Effects):

- Short-latency stretch reflex excitability.
- Trunk muscle onset latencies in response to postural perturbations.
- Lumbar motion during volitional movement tasks.
- Dynamic trunk stiffness
- Group 3 (Cortical Effects):
  - Motor evoked potential amplitude.
  - Intracortical facilitation.
  - Short-interval intracortical inhibition.

### RCT Component

#### Co-Primary Outcomes:

- Change in Numerical Pain Rating (NPR) score for average over the last 7-days
- Change in Roland Morris Disability Questionnaire (RMDQ)

#### Secondary Outcomes:

- Change in PROMIS Pain Behavior
- Change in PROMIS Pain Interference
- Change in PROMIS Pain Intensity
- Change in PROMIS Physical Function
- Change in NPR scores for current pain, and worst and best pain in the last 7-days

The primary endpoint will be OA3.

## **9.5 Data Analyses**

Here we describe three stages at which both the Mechanistic and RCT data will be analyzed in the same fashion: preliminary analysis, checking assumptions, and detailed analytic approach. Data analysis regarding the supplemental research is included in the appendix.

### **Preliminary Analysis:**

- At the first preliminary-analysis stage, we will examine whether the randomization is successful (i.e., the means for the three treatment arms do not differ in demographic variables or health characteristics) by using  $\chi^2$  tests for categorical variables and one-way ANOVAs for continuous variables. If significant differences in the demographic variables or health characteristics emerge, they will be treated as covariates in a model at the second stage. The effect of random factors (i.e., the blocks and treatment providers) will also be examined. If the variances of these factors were not significant at a liberal alpha level of 0.20, they will be excluded from further analysis. However, if a significant block and/or treatment-provider effect is detected, this will be included as a random effect in the model at the second stage. Likewise, we will perform an ANOVA to evaluate whether the means for the three mechanistic experiments differ in the clinical outcome variables. If the experiment factor is significant, this factor will be included as a fixed effect in further analysis. Otherwise, clinical outcome data will be pooled across the experiments.

- We will use means and standard deviations as the primary descriptive statistics for continuous variables and proportions for categorical variables. If variables are skewed, medians and interquartile ranges will be used. We will also compute pairwise correlation between a pair of endpoints as well as autocorrelations through all endpoints for each outcome measure. We will compute confidence intervals around the means as well as effect-size indices (e.g., Cohen's d for two-group comparisons and f for multiple-group comparisons) and confidence intervals around the effect sizes.

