- Randomization & Stratification: The study statistician will use the R statistical language to block-randomize treatments stratified by sex for each of the three separate experiments. Specifically, within each experiment there will be two strata within which we will create blocks of 3 patients, where treatments are permuted. Based on the randomization table the study coordinator will assign subjects to the treatment arms. In instances where multiple experiments are actively enrolling study participants and a participant meets eligibility requirements for more than one experiment, we will then use an adaptive randomization method to allocate them to one of the experiments. This method ensures that an experiment with fewer participants enrolled will have a higher allocation ratio. Specifically, with two potential experiments, the allocation ratio for Experiment  $i$  ( $p_i$ ) will be  $p_i = 1 - n_i/N$ , where  $n_i$  is the sample size for Experiment  $i$  and  $N$  is the total sample size thus far enrolled. With three active experiments, the allocation ratio will be  $p_i = (1 - n_i/N)/2$ . Note that this allocation to an experimental measurement group occurs prior to the randomization to a treatment arm.
- Masking or Blinding: In the RELIEF Study the principal investigators, the statistician, and members of the data collection team will remain blinded to intervention assignment throughout the duration of the study. They will be given the identifying codes only at the end of the study when it is necessary to interpret the results of the study. The un-blinded study coordinator, who is responsible for scheduling testing and treatment sessions, will serve to receive the study patients and escort them to the various testing and treatments sites to minimize the interaction between patients; however, the study coordinator will not participate in the assessments.

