### **Detailed Analytic Approach:**

Linear mixed-effects regression (LMER) analyses will serve as the main analytic framework, because it offers distinct advantages in statistical power and estimation of population parameters over ANOVA or MANOVA. First, LMER easily incorporates miscellaneous factors (e.g., blocks and treatment providers) as random effects so that the variances due to those factors can be partitioned. As a result, LMER models typically offer less biased parameter estimation and can also offer higher statistical power. It can model multiple dependent variables (e.g., motor evoked potential amplitude, intracortical facilitation, and short-interval intracortical inhibition for Group 3) and test the effect of treatment for each of these dependent variables simultaneously. This modeling technique avoids alpha inflations which typically result from multiple testing. Finally, LMER's maximum-likelihood estimation allows patients with missing observations to be included in a model if the observations are missing completely at random or missing at random. This advantage is important because some degree of attrition is unavoidable given the longitudinal nature of our project. Because we will stratify our samples by sex, sex will be included in each of the models we will describe below. We will test the significant main effect of sex as well as its interaction with the Treatment factor.

- **Intention to Treat Analysis (ITT):** We will include all randomized study participants who have at least baseline endpoint assessments in our ITT analysis. The ITT analysis is our primary method for assessing outcomes, and how it is performed will be determined based on the pattern of

missingness. If the missingness is deemed MCAR, the LOCF method will be used: simply the most recent valid observation will be "carried forward" to replace the subsequent missing observations. If the missingness is deemed MAR, missing observations will remain as missing, and maximum-likelihood estimation, the default estimation algorithm of LMER, will be used to estimate these observations. If the missingness is found to be MNAR, multiple-imputed data will be used to construct LMER models.

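### The RCT model always includes sex because it is a stratifier, but includes experiment, also a stratifier, only after a significant pre-test, and picks other covariates by baseline imbalance

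*Supplement*

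**What the plan says.** **Randomization.** Section 3 has the statistician "block-randomize treatments stratified by sex for each of the three separate experiments", and adds: "Specifically, within each experiment there will be two strata within which we will create blocks of 3 patients, where treatments are permuted". Section 4.3 repeats this, as does Treatment Assignment Procedures in 9.2, which gives blocks of 3 or 6. Experiment by sex therefore defines six strata.

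**Sex.** Section 9.5, Detailed Analytic Approach: "Because we will stratify our samples by sex, sex will be included in each of the models we will describe below".

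**Experiment.** Section 9.5, Preliminary Analysis, plans an ANOVA of the clinical outcomes across the three experiments. "If the experiment factor is significant, this factor will be included as a fixed effect in further analysis". When that test is negative, the factor is left out and the three experiments are combined. The RCT paragraphs of 9.1 and 9.5 say only that the clinical data are collapsed across the three groups.

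**Other terms.** After chi-square tests and one-way ANOVAs between arms: "If significant differences in the demographic variables or health characteristics emerge, they will be treated as covariates in a model at the second stage". For blocks and treatment providers: "If the variances of these factors were not significant at a liberal alpha level of 0.20, they will be excluded from further analysis".

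**Fixed in advance.** The baseline value of the outcome is in the RCT models unconditionally (9.1 and 9.5), as is sex.

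**The concern.** Experiment and sex have the same standing in the randomization but opposite treatment in the analysis. The reason the plan gives for always modelling sex applies equally to experiment.

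The pre-test is also under-defined. Its significance level is not stated: the experiment sentence is introduced as parallel to the block and provider rule, which uses 0.20, while the end of 9.5 sets 0.05 for all analyses. The time point of the ANOVA is not stated. Nor is it clear whether one result governs both co-primary outcomes, so NPR and RMDQ could end up with different models.

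The covariate rule has a separate fault. Once arms are randomized, a significant baseline difference between them reflects chance. Selecting on it can admit a variable unrelated to outcome and leave out a strong predictor that happens to be balanced. The variables to be tested are not listed.

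At stake is whether two analysts following 9.5 would fit the same primary model, and whether the standard error reflects the way patients were randomized.

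**Working it through.** **1. The plan's own figure.** Section 9.2 gives power 0.80 with 54 per arm, d = 0.5 and 10% attrition.
- n = 54 × 0.9 = 48.6 per arm, and d·√(n/2) = 0.5 × √24.3 = 2.465.
- One-sided 0.05: Φ(2.465 − 1.645) = 0.794, which reproduces the 0.80.
- Two-sided 0.05: Φ(2.465 − 1.960) = 0.693. With an assumed baseline correlation of 0.5, 2.465/√0.75 = 2.846 and Φ(0.886) = 0.812.

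The one-tailed (9.1) versus two-tailed (9.5) conflict affects this line, not the point here.

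**2. How often the pre-test keeps a real experiment effect.** Noncentral F with 2 and 159 df, λ = 162·f². The f values are assumptions.

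| f | kept, alpha 0.05 | kept, alpha 0.20 | SE increase if dropped, √(1+f²) − 1 |
|---|---|---|---|
| 0.10 | 0.19 | 0.43 | 0.5% |
| 0.15 | 0.38 | 0.65 | 1.1% |
| 0.20 | 0.61 | 0.84 | 2.0% |

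**3. What the pre-test costs the treatment comparison.** Simulation: 3 arms by 3 experiments (14/20/20 per arm), baseline correlation 0.5, no dropout, two-sided 0.05, pre-test alpha 0.05, d = 0.5 for power, 6,000 runs per scenario. The correlation, the pre-test alpha and the experiment effects (in SD units) are assumptions, because the documents give none.

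| Experiment effects | Factor kept | Mean SE: always / pre-test | Power: always / pre-test / never | Type I error: pre-test / never |
|---|---|---|---|---|
| 0 | about 4–5% | 0.167 / 0.167 | 0.848 / 0.848 / 0.848 | 0.051 / 0.051 |
| +0.2, 0, −0.2 | 38–41% | 0.1668 / 0.1677 | 0.848 / 0.847 / 0.841 | 0.046 / 0.043 |
| +0.4, 0, −0.4 | about 95% | 0.1670 / 0.1672 | 0.841 / 0.841 / 0.814 | 0.045 / 0.033 |
| +0.6, 0, −0.6 | about 100% | 0.1669 / 0.1669 | 0.842 / 0.842 / 0.772 | 0.051 / 0.028 |

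The largest SE penalty of the pre-test is 0.1677/0.1668 − 1 = 0.5%.

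**4. Closed-form check of collapsing at ±0.4.** Experiment shares are 42, 60 and 60 of 162, so the between-experiment variance is 0.0988.
- Adjusted SE = √(0.75 × 2/54) = 0.1667. Unadjusted SE = √((0.75 + 0.0988) × 2/54) = 0.1773, which is 6.4% larger.
- Randomization balances experiment across arms, so the true variability stays at 0.1667. The actual type I error is then 2·[1 − Φ(1.96 × 0.1773/0.1667)] = 0.037, against 0.033 simulated.

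**5. Chance entry of covariates.** 1 − 0.95^k, for k independent tests: k = 5 gives 23%, k = 10 gives 40%, k = 15 gives 54%. Both k and independence are assumptions.

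**6. Cost of always adjusting.** 162 − 1 (intercept) − 2 (treatment) − 1 (baseline) − 1 (sex) − 2 (experiment) = 155 residual df.

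**The case against.** The strongest reply is that little harm follows. The factor is dropped mainly when its effect is small, so the low pre-test powers in step 2 do not translate into lost power for treatment. That stands. A reader might infer from a retention rate of 0.19 that precision is seriously lost; steps 2 and 3 do not support this, and at a pre-test alpha of 0.20 the factor is kept more often still.

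A reader might also infer that data-driven model choice inflates false positives. The checks do not show it. Type I error under the experiment pre-test is 0.045 to 0.051. A simulation of the covariate rule (10 independent covariates, two prognostic with assumed correlation 0, 0.3 or 0.5) gave 0.049, 0.046 and 0.042. A covariate admitted by chance costs a degree of freedom and does not bias a randomized comparison.

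Nor are all covariates chosen by test: sex and baseline outcome are fixed. Blocks are nested within strata, so a retained block effect would absorb part of an experiment difference, but blocks are themselves kept only after a test.

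It is also fair that differences between experiments are not established. All back-pain participants share the same pain, disability and prediction-rule criteria, and those eligible for several open experiments are allocated among them at random. Against that, eligibility differs by experiment (magnetic-field, seizure, migraine and benzodiazepine rules), so differences are possible. Finally, the RCT component is exploratory, the rule is written down in advance and the statistician is blinded. This limits the seriousness but does not remove the inconsistency with sex.

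**Conclusion.** The point holds as one of specification and consistency, not of material loss. A stratification factor is subject to a pre-test that the plan's own reasoning for sex would rule out. The pre-test's alpha and timing are open, and the covariate rule selects on chance imbalance (23% to 54% chance of at least one such entry for 5 to 15 independent tests at 0.05).

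Under the assumptions of step 3, the pre-test costs at most about 0.5% in mean SE and about 0.2 percentage points of power, with type I error near nominal. The size is larger only if the data are collapsed with no adjustment, which is the literal wording of the RCT paragraphs in 9.1 and 9.5. At assumed experiment effects of ±0.4 SD, power then falls from about 0.84 to about 0.81 and type I error to about 0.035, an error in the conservative direction. This is a free improvement.

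**What to change.** In 9.5, state that every RCT model includes treatment, the baseline value of the outcome, sex and experiment (three levels) as fixed effects, whatever any preliminary test shows. Delete the ANOVA on experiment as a condition for pooling, and delete the between-arm baseline tests as a rule for choosing covariates. Present baseline characteristics descriptively by arm. If any further prognostic covariate is wanted, name it before unblinding. A treatment-by-experiment summary can be reported descriptively as a check on pooling.

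Align the RCT paragraphs of 9.1 and 9.5 with this, so that collapsing means combining the three experiments in one model that contains experiment. The cost is a change of wording and 2 of about 155 residual degrees of freedom; design, sample size and data collection are unaffected.
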